**Secondary Outcomes Analyses:** Our secondary patient-reported outcomes are changes in HRQOL (SF-12 mental and physical component score) in TACCare versus control arm after a 12-week intervention. EMA-measured composite symptom severity score will be evaluated at baseline and post-intervention (12 weeks). Adherence outcomes include adherence to medications, diet and dialysis treatments (all continuous variables) measured at 12-weeks, and at 6-and 12-months follow-up. Biomarkers of inflammation include hs-CRP, IL-6, IL-10, and TNF- $\alpha$  measured at baseline, 12-week, and 6-months follow-up. GLMM will also be used to analyze these outcomes. Benjamini-Hochberg correction will be applied to the biomarker analyses. We will also assess the bi-directional association and calculate correlations between the biomarkers and symptoms. Moreover, we will examine how adjusting for the biomarkers influences the TACCare effect on the symptoms, and how adjusting for the symptoms influences the effect on the biomarkers.

**Subgroup Analyses:** The response to treatment interventions may differ among certain patient subgroups. Thus, to explore heterogeneity of intervention effects, we will examine pre-specified subgroups including age – age $\leq$ 65, age $>$ 65; sex – male, female; race – white, black, others; Charlson comorbidity index – less than 4, 4 or more; and dialysis vintage  $\leq$  1 year, vintage  $>$  1 year. Each variable, its two- and three-way interaction with the treatment group and with time were added to the model, and linear contrasts were used to test for heterogeneity of treatment effects. In addition, we will estimate the treatment effects among those who had elevated symptoms at baseline (FACIT-F $\leq$ 44, BDI $\geq$ 16, BPI $\geq$ 5).

**Sensitivity analyses:** We will perform additional analyses to assess the robustness and potentially refine our conclusions. This would include assessing intervention as-treated rather than intention-to-treat, nonlinearity of time in the EMA fatigue model, impact of outliers or influential points and impact of missing data.

**Intercurrent events (ICE):** To maintain a consistent approach, we have selected a hypothetical strategy as our primary approach to handle all ICEs (death, Kidney transplant, switching to home dialysis, patient relocated, withdrawal, treatment dropout/discontinuation, treatment paused due to COVID) to estimate what would have been the outcome at the follow-up time points had the ICE did not occur. Thus, only data that were observed prior to the occurrence of the ICE will be used in fitting mix models for the primary analyses. We opted to keep using mixed models as the primary analytic approach to execute the hypothetical strategy to take advantage of the longitudinal data collection and hence makes more efficient use of available data. This approach assumes post-ICE outcomes can be predicted using observed pre-ICE outcomes and other measured characteristics.

**Missing Data:** The extent, reasons, randomness of missing data will be examined to identify possible covert missing data mechanisms. Baseline characteristics and intermediate outcomes among those who do or do not complete the study will be compared. The primary analytical approaches (GLMM) can handle data that are ignorably missing (i.e., either missing completely at random or missing at random). However, strategies to handle missing data (single/multiple imputation, selection models, pattern-mixture models, etc.) and sensitivity analyses to encompass different scenarios of assumptions will be considered as appropriate. For measures that were missing due to non-response at the item-level, multiple imputation by chained equations will be used to impute the response at the item level. The median value across 5 imputed datasets will be used in the calculation of overall score.

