**Randomization:** After completion of baseline assessments (as below), the Study Coordinating Center will randomly assign patients in 1:1 ratio to either TASCCI or health education arm, using a pseudo-random number generator. Randomization will be stratified by the two clinical sites, age ( $< 60$  and  $\geq 60$  years) and Charlson comorbidity index ( $< 4$  and  $\geq 4$ ) to achieve equal distribution of these potentially confounding variables between the two arms. Randomly-permuted blocks will be used to help balance numbers of participants assigned to each intervention. Patients in both arms will receive an intervention delivered using video-conferencing. Thus, even though patients at outpatient dialysis clinics are in close proximity to fellow patients, we expect that any chances of cross-contamination between study arms is minimal. Moreover, even if the patients in different arms at the same unit interact with each other, these interactions are likely to be brief and unlikely to have any sustained effect on our outcomes of interest. Moreover, the care coordinator for the intervention and control arm will not be the same person to ensure there is no unintentional contamination from the study staff while delivering the intervention. Lastly, although there is a possibility that the renal providers start recognizing and recommending symptom management in the control arm patients, this is unlikely given reluctance of patients and providers regarding pharmacotherapy alone, and patient burden associated with in-office CBT.

**Allocation concealment and blinding:** Neither the patients nor the PI can be blinded due to the nature of the study intervention. However, research staff assessing patient-centered outcomes will be blinded to the group assignment.

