**Measuring Selected Pro/anti-inflammatory Cytokines:** Selected cytokines (*high sensitivity C - reactive protein; hs-CRP, Interleukin; IL-6, IL-10 and Tumor Necrosis Factor; TNF- $\alpha$* ) were chosen based on their reported associations with the outcomes of interest. All blood samples will be shipped at regular intervals and cytokine measurements will be performed centrally at the University of Pittsburgh. We will collect 10ml of blood drawn pre-dialysis at baseline, post 12-week intervention and at 6-month follow-up. Serum will be aliquoted within 4 hours of the blood draw, shipped on dry ice and stored at -80°C for batch analysis. Cytokine levels will be measuring using Luminex™ bead-set (Millipore Corporation, Billerica MA and Luminex™ 100 IS apparatus, Austin TX) in accordance with the manufacturer's instructions using standardized validated assays and operating procedures.

**Descriptors and Potential Covariates:** Baseline patient data collection will include socio-demographic data such as age, gender, race, ethnicity, education, marital and employment status, household income, etc. The patient's clinical characteristic such as years on dialysis, comorbid conditions, concomitant medications, etc.

along with data on hospitalizations, mortality and transplantation will be obtained from patient interviews and medical chart abstraction. Routine monthly laboratory assessment done by the dialysis clinics will be extracted.

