## Summary of Major Revisions to the SAP

1. To gain efficiency, primary analyses adjusted for variables used in stratification as detailed in the design paper (October 2018). Prior to study results unblinding to the study team on August 25, 2022, sex was also added to the model.
2. Subgroup analyses based on charlson comorbidity were made consistent with the cutpoint used in the stratified randomization (CCI $<$ 4 and CCI $\geq$ 4) as detailed in the design paper (October 2018).

Subgroups based on elevated symptom at baseline were also examined to determine if the treatment effects could be different among those who have elevated symptoms at baseline. This was added prior to the study results unblinding to the study team on August 25, 2022.

3. Item-level imputation was performed prior to calculating scores to minimize missing data. This plan was added prior to study results unblinding to the study team on August 25, 2022.
4. To handle intercurrent events (ICE), the estimands approach from the ICH E9 R1 was adopted [Mallinckrodt CH, Bell J, Liu G, Ratitch B, O'Kelly M, Lipkovich I, Singh P, Xu L, Molenberghs G. Aligning Estimators With Estimands in Clinical Trials: Putting the ICH E9(R1) Guidelines Into Practice. *Ther Innov Regul Sci*. 2020 Mar;54(2):353-364. doi: 10.1007/s43441-019-00063-9. Epub 2020 Jan 6. PMID: 32072593]. This was suggested by an NIDDK biostatistician when the study size was requested to be increased. (September 2020)
5. Due to lack of access to Morisky medication adherence scale which will be used to define the per-protocol set, the per-protocol analyses were not performed.
6. A joint longitudinal model was also used as an alternative model for the three primary outcomes as recommended by the biostatistical reviewer. (March 2023)

| Patient-Reported Outcome (PRO) instruments (Appendix)                                                    |              |                                                             |                                                                                                                                                                                                                                                                                   |

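### Effect heterogeneity by age, Charlson index and dialysis vintage is tested only through two-level cuts; adding the continuous versions would recover information in exploratory tests that are already weak

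*Protocol*

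**What the plan says.** The aim is exploratory: "to explore heterogeneity of intervention effects, we will examine pre-specified subgroups including age", followed by sex, race, Charlson index and vintage. Age is split at 65 and the other two numeric variables as "less than 4, 4 or more; and dialysis vintage" at 1 year. Each variable enters with its two- and three-way interactions with treatment and time, and "linear contrasts were used to test for heterogeneity of treatment effects".

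The underlying values are collected. Under Descriptors and Potential Covariates, the baseline data include "socio-demographic data such as age, gender, race, ethnicity" and the "clinical characteristic such as years on dialysis, comorbid conditions". A numeric Charlson score is not named there, but Randomization stratifies on the index at 4, so a score must exist.

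One cut has a stated origin. The Summary of Major Revisions to the SAP records that "Subgroup analyses based on charlson comorbidity were made consistent with the cutpoint used in the stratified randomization". For age, the Randomization paragraph ("Randomization will be stratified by the two clinical sites, age") uses 60 years while the subgroup cut is 65, and no reason for 65 is given. No reason is given for the 1-year vintage cut either.

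Neither the sensitivity analyses nor the list of revisions contains a version with these variables as continuous terms.

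**The concern.** A two-level cut treats patients just either side of it as different, and patients far apart on the same side as identical. For vintage this is marked. Entry requires more than 3 months of hemodialysis, so the shorter group spans only about months 3 to 12, while every longer duration falls into one group.

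If the effect of the intervention changes gradually with age, comorbidity or time on dialysis, the split test sees only part of that gradient. Interaction tests at this sample size are weak to begin with. What is at stake is whether an exploratory analysis uses the data already collected. The primary comparison is untouched.

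**Working it through.** **Inputs from the protocol.** Effective sample size 136, 1:1 allocation, two-sided 5% tests, planned effect 0.6 SD. The revised target gives 160 × 0.86 = 137.6, which barely changes the results below. The protocol states no distribution, subgroup share or power for the subgroup tests.

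**The plan's own figure.** The only power stated is for the main comparison. At 68 per arm and effect size 0.6, a two-sided t-test gives 93.5% (stated 93%). A simulated Benjamini-Hochberg procedure with one true effect among three independent endpoints gives 86.1% (stated 88%). The sample-size base is therefore sound.

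**Weakness of the planned split tests.** With a share p in one group, the standard error of the difference in effect is √(4/(136·p(1−p))).
- 50/50: √(4/34) = 0.343. For a difference of 0.6 SD, power = Φ(0.6/0.343 − 1.96) = 42%.
- 30/70: standard error 0.374, power 36%.
- 20/80: standard error 0.429, power 29%.

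So a difference between groups as large as the whole planned effect would be detected 29% to 42% of the time. The difference detectable with 80% power is 0.96 SD (50/50) to 1.20 SD (20/80).

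**Information kept after a cut.** Assume a normal modifier with a linear interaction. The share kept is r² = φ(z_p)²/(p(1−p)).
- 50/50: 0.3989²/0.25 = 0.637, a loss of 36%.
- 30/70: 0.576, a loss of 42%.
- 20/80: 0.2800²/0.16 = 0.490, a loss of 51%.

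In effective patients, 136 becomes about 87 at 50/50 (136 × 0.637) and about 67 at 20/80 (136 × 0.490).

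**Power, continuous against split.** The standard error of the interaction slope per covariate SD is 2/√136 = 0.171. Splitting multiplies the expected z-value by r, which is 0.798 at 50/50 and 0.700 at 20/80. Power is Φ(z − 1.96).

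| Assumed slope (outcome SD per covariate SD) | Continuous | 50/50 cut | 20/80 cut |
|---|---|---|---|
| 0.4 | z = 2.33, 65% | z = 1.86, 46% | z = 1.63, 37% |
| 0.2 | z = 1.17, 21% | z = 0.93, 15% | z = 0.82, 13% |

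**How far the loss depends on the distribution.** All distributions here are assumptions.
- Age, normal with mean 55 to 65 and SD 12 to 15, cut at 65: loss 36% to 52%.
- Charlson, as 2 plus a Poisson count with mean 1 to 4, cut at 4: loss 30% to 74%.
- Vintage, right-skewed and cut at 1 year: loss 34% to 71% if the effect is linear in log years, 66% to 96% if linear in years.

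**The case against.** The strongest reply is that pre-specified, exploratory two-level subgroups, tested by interaction rather than by separate within-group tests, are ordinary practice and contradict nothing in the protocol. Several parts of that reply stand.

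- A reader might infer that 36% to 51% is the loss for all three variables. The protocol does not support that. The range needs a normal modifier, a linear effect and a split between 50/50 and 20/80, and no distributions are given. Only age fits it roughly under the assumptions tried. A threshold effect near a cut would shrink the loss.
- A reader might infer that the cuts serve no purpose. For Charlson this is wrong: the cut was deliberately matched to the randomisation stratum.
- A reader might infer that a non-significant split test will be reported as absence of heterogeneity. Nothing in the protocol says so.
- A slope of 0.4 is generous. Patients one SD above and one SD below the mean would differ by 2 × 0.4 = 0.8 SD in effect, more than the planned 0.6. At 0.2 the gain is only about 6 to 9 points (21.4 − 15.2 = 6.2; 21.4 − 12.6 = 8.7).
- The standard errors are for a single-time comparison. The planned test is a contrast from a longitudinal model with random intercepts and covariates, so the absolute powers are only indicative.
- Results were unblinded to the study team on 25 August 2022, so the change may no longer be prospective.

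These points limit the size of the claim and turn the remedy into an addition rather than a replacement. They do not remove the fact that numeric information already collected goes unused in tests that are weak.

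**Conclusion.** The point holds as a minor improvement. Heterogeneity by three numeric variables is tested only after splitting each in two, the values are available, and no continuous analysis is stated. For a roughly normal, linearly acting modifier the loss is about 36% at a 50/50 split and 51% at 20/80. It may be larger for vintage, and smaller under a threshold effect.

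With 136 patients, continuous terms would raise power from 46% or 37% to about 65% at an assumed slope of 0.4, and from 15% or 13% to about 21% at 0.2. It would be wrong to conclude that this makes the heterogeneity tests adequate. Even in the favourable case they stay below 80%, so a null result remains inconclusive under either approach.

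**What to change.** In the Subgroup Analyses paragraph, add treatment-by-time-by-covariate interactions with age, Charlson index and log vintage as continuous terms. Read heterogeneity from them at 12 weeks and check linearity, for example with one added quadratic term. Keep the listed two-level groups, including the Charlson cut aligned with the randomisation stratum, for presenting estimates. Sex and race stay categorical.

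The cost is one sentence and a few lines of code, with no new data. The downsides are the linearity assumption and timing: if added after the August 2022 unblinding, the analysis must be labelled post hoc and supplementary to the pre-specified group comparisons.

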### **Original Statistical Analysis Plan**

**Sample Size and Power:** We powered our study to detect a clinically meaningful difference in our primary outcomes -- depression, pain, or fatigue -- for Aim 1 at 12 weeks while considering feasibility of subject recruitment. Since there is no validated composite endpoint consisting of the 3 outcomes, we will test the effect of TASCCI on each of the outcomes. We calculated power controlling for False Discovery Rate (FDR) of 5% using the Benjamini-Hochberg correction. To be more conservative, (1) we used a two-sided two-sample t-test in the calculations and (2) assumed that the intervention has a true effect on exactly one endpoint.

Our primary analysis will compare groups at 12 weeks using contrast from a mixed model that includes all time points (baseline, 12 weeks, 6 months, and 12 months). By using all available longitudinal data, our primary analytical approach would be more efficient than t-test and provide greater power to detect differences. We will also have increased power if the intervention has real effect on more than one endpoint.

The projected total sample size is 150, or 75 per group. After accounting for the estimated 10% lost-to-follow-up, the effective total sample size is 136. For this sample size, Table 1 shows the estimated power for a range of effect sizes (standardized mean difference) with and without adjusting for FDR using PASS 13 (NCSS, LLC, Kaysville, UT)

**Table 1:** Estimated power for total sample size of  $N = 136$  for a range of effect sizes with and without adjusting for a 5% false discovery rate (FDR).

| Effect Size
(Standardized Mean
Difference) | FDR-
unadjusted | FDR-adjusted |             |
|--------------------------------------------------|--------------------|--------------|-------------|
|                                                  |                    | 3 endpoints  | 4 endpoints |
| 0.4                                              | 64%                | 40%          | 32%         |
| 0.5                                              | 82%                | 70%          | 63%         |
| 0.6                                       | 93%         | 88%   | 85%  |
| 0.7                                              | 98%                | 96%          | 95%         |
| 0.8                                              | 100%               | 99%          | 99%         |

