Thus, our sample size provides 88% power to detect an effect size of 0.6 controlling for 5% FDR for 3 endpoints assuming a true difference exists in 1 out of 3 endpoints. If differences exist on 2 of 3 endpoints, we will have 89% power to detect an effect size of 0.5. The detectable effect size is consistent with what we observed in our study of SCCI in cancer patients (effect size was 0.7 for depression, 0.6 for pain and 0.3 for fatigue, respectively).

In May 2020, the sample size was increased to 160 participants per DSMB recommendations given a higher observed attrition rate (14%).

**General Statistical Approach:** Distributions of baseline characteristics will be compared between the groups to assess effectiveness of randomization, and statistical differences will be accounted for as covariate in secondary adjusted analyses. All primary analyses will be adjusted for site, age, and comorbidity (design variables) as well as sex and unadjusted analyses will also be reported per CONSORT recommendations. The stratification variables are potentially prognostic of the outcomes, which likely will make the adjusted analyses more efficient than unadjusted. The primary analyses will use the 'intent-to-treat' approach in which subjects are analyzed in their assigned group, regardless of treatment adherence, withdrawal or deviation from protocol. General linear mixed models (GLMM) will be used for inferential analyses of primary and secondary outcomes. Unless otherwise specified, all tests will be conducted using two sided 5% level of significance. We will report our findings according to the CONSORT guidelines.

**Preliminary Analyses** will focus on data checks for completeness and accuracy and address any issues with data quality. The preliminary exploration of the data will be used to: 1) examine univariate and bivariate distributions; 2) identify any imbalances between treatment groups on baseline characteristics; 3) investigate the magnitude of the associations between the dependent variables and the potential covariates; 4) verify the statistical assumptions of the planned primary analyses. If assumptions are violated, then alternative procedures such as data transformations or more robust statistical methods will be considered.

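### The elevated-symptom subgroups were added to see whether the effect differs, but the plan states only an estimate within the elevated patients and no contrast with the rest

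*Protocol*

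**What the plan says.** The Subgroup Analyses paragraph of the Protocol (section Original Statistical Analysis Plan) presents its aim as exploring heterogeneity of the intervention effect. It names age, sex, race, Charlson comorbidity index and dialysis vintage. Each is entered with its two- and three-way interactions with arm and time, and "linear contrasts were used to test for heterogeneity of treatment effects".

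The next sentence turns to baseline severity: "In addition, we will estimate the treatment effects among those who had elevated symptoms at baseline". The cut-offs are FACIT-F at most 44, BDI at least 16 and BPI at least 5. No interaction term, estimate in the remaining patients or contrast is mentioned.

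The purpose appears in the Summary of Major Revisions to the SAP, under item 2. These subgroups were "examined to determine if the treatment effects could be different among those who have elevated symptoms at baseline", and they were added before the study team was unblinded on August 25, 2022.

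**The concern.** Whether effects differ by baseline severity is a question about two groups: the null is that the effect in elevated patients equals the effect in the others. An estimate among elevated patients, with its confidence interval, speaks to whether there is an effect in that group. It carries no information about the others. Setting it beside the overall effect does not repair this, because the overall sample contains the subset.

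The comparison group should exist. Under Screening, a patient qualifies with a clinical level of any one of three symptoms. Under Primary Outcomes Analyses, all three outcomes are analysed in every patient. Patients below the cut-off on a given instrument are therefore to be expected.

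At stake is what the report may say about who benefits. A clear effect in the elevated subset could be taken as specific to those patients when it is the same in everyone. An unclear one could be taken as absence of benefit when the subset is merely small.

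**Working it through.** **Inputs from the Protocol**
- Test level: "all tests will be conducted using two sided 5% level of significance".
- Evaluable patients: "After accounting for the estimated 10% lost-to-follow-up, the effective total sample size is 136", which is 68 per arm.
- Allocation: 1:1 (Randomization).
- Design effect: 0.6 SD, with a two-sided two-sample t-test (Sample Size and Power).
- Revised target: 160 with 14% attrition, so 160 × 0.86 ≈ 138 evaluable.

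**Assumed, because the Protocol does not give it:** the share f of patients elevated on a given instrument, taken as 30%, 50% or 60%; equal variances; even allocation within strata.

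**1. The plan's own figure.** Two-sided t-test, 68 per arm, effect 0.6:
- noncentrality = 0.6 × √(68/2) = 3.50
- power from the non-central t = 93.5%, against 93% in the FDR-unadjusted column of Table 1. The design figure is reproduced.

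**2. Subset alone, same effect of 0.6 SD in everyone.** Patients per arm in the subset = 136f/2 = 68f; noncentrality = 0.6 × √(68f/2); df = 136f − 2.

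| Assumed share elevated | Per arm in subset | Noncentrality | Probability that the subset is significant |
|---|---|---|---|
| 30% | 20.4 | 1.92 | 46% |
| 50% | 34.0 | 2.47 | 68% |
| 60% | 40.8 | 2.71 | 76% |

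With 138 evaluable the values are 47%, 69% and 77%. The true difference between elevated and other patients is zero in every row. The subset result therefore depends on the size of the common effect and the size of the subset, not on heterogeneity.

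**3. The contrast that matches the question.** In SD units, the standard error of the elevated-minus-other difference in effects is √(4/(Nf) + 4/(N(1 − f))).
- N = 138, f = 0.5: √(4/69 + 4/69) = 0.341.
- Equal effects: rejects in 5% of trials by construction.
- True difference of 0.6 SD: power ≈ Φ(0.6/0.341 − 1.96) = 42%.
- Difference detectable with 80% power: 2.80 × 0.341 ≈ 0.95 SD.
- At f = 0.3 the corresponding values are 37% and 1.04 SD.

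These are t-test and normal approximations, not the planned mixed model.

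**The case against.** The strongest reply is that the sentence promises an estimate and nothing more. It sets no test of the subset against zero, no decision rule and no claim that effects differ. Estimating the effect in symptomatic patients is a sound aim in itself, since a patient who enters on one symptom may have little room to improve on another scale. This stands, and it limits what the figures mean. The 46%, 68% and 76% are legitimate power for detecting a real effect in the subset, and rejecting zero there would be correct. A reader might infer that they are false-positive rates to be set against 5%, or that the plan will declare an effect found only in elevated patients. Neither follows: the two tests have different nulls, and a finding of significance in the elevated but not in the rest would need a test in the rest that the plan does not state.

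Second, the explicit purpose comes from a summary of revisions. That summary describes text that was added, not text that was replaced, so it explains why the current sentence is there. The subgroup paragraph itself also opens with heterogeneity as its aim.

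Third, the interaction sentence might be meant to cover elevated status too, or a separate analysis plan might specify it. Either is possible, so one cannot say that patients without elevation are certain to be left out. But the interaction sentence refers back to the five listed variables, and elevated status follows it as an addition with its own method. If interactions were intended, the same short edit makes that clear.

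Finally, the contrast has low power. That is true, and it is a reason to show the difference with its interval, not to omit it.

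**Conclusion.** The point holds in a limited form. The stated purpose is to learn whether effects differ in patients with elevated symptoms; the stated method is an estimate in those patients alone, which cannot show that. The same paragraph already contains the method that can.

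The size depends on an elevated share that the Protocol does not give, and on how the result is read. Under a uniform effect of 0.6 SD, a significant subset result is expected in roughly half to three quarters of trials for shares of 30% to 60%, so it says little about whether the effect differs. The analysis is exploratory, was added before unblinding, and touches neither the primary 12-week contrast nor its false-discovery-rate control. It is an inexpensive improvement to consider, not a defect that threatens the trial's conclusions.

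**What to change.** In the Subgroup Analyses paragraph, extend the existing interaction sentence to baseline elevated status (yes or no), defined for each outcome by its own cut-off. Report the 12-week effect in both the elevated and the not-elevated stratum, with the difference between them and its 95% confidence interval. Add that any statement that effects differ by baseline severity rests on that difference alone. The estimate among elevated patients stays as one of the two stratum estimates.

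The cost is about a sentence of wording and three more exploratory contrasts, one per primary outcome, with no new data. The intervals will be wide: at an even split with 138 patients the 95% half-width is about 1.96 × 0.341 = 0.67 SD. A non-significant contrast should therefore not be reported as evidence that effects are equal.

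### The as-treated comparison is not a valid robustness check on the intention-to-treat result; it can show a benefit without a true effect if non-engaged patients have a worse 12-week change

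*Protocol*

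**What the plan says.** In the protocol's Original Statistical Analysis Plan, the Sensitivity analyses paragraph opens: "We will perform additional analyses to assess the robustness and potentially refine our conclusions". The as-treated comparison is the first item listed: "assessing intervention as-treated rather than intention-to-treat". Nonlinearity of time in the EMA model, outliers and missing data follow.

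Three other places bear on it:

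- General Statistical Approach sets the primary analysis by randomised arm: "subjects are analyzed in their assigned group, regardless of treatment adherence, withdrawal or deviation from protocol".
- Intercurrent events adopts a hypothetical strategy that covers treatment discontinuation: "only data that were observed prior to the occurrence of the ICE will be used in fitting mix models for the primary analyses".
- Summary of Major Revisions to the SAP records that "the per-protocol analyses were not performed", but does not withdraw the as-treated analysis.

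**The concern.** Whether a patient counts as treated is settled after randomisation, by attendance and willingness to continue. The protocol gives reasons to think that this is related to prognosis. Its Background links depression, pain and fatigue to non-adherence, and its section on duration of intervention has patients re-assessed for ability and interest to continue after acute illness. Taking non-engaged patients out of the TACcare group can therefore leave a group with a better outlook than the one randomised.

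A sensitivity analysis should keep the question and vary an assumption behind the answer. An as-treated comparison changes the question. If it agrees with the main result, no assumption of that result has been tested; if it disagrees, the cause may be selection alone. What is at stake is false reassurance, or a conclusion refined on a confounded comparison.

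**Working it through.** **Plan's own figures.** The plan states no figure for the as-treated analysis. Its power statement reproduces without it. With 68 per arm (136 in total), a standardised difference of 0.6 and two-sided 5%, the noncentral t gives 93.5% (plan: 93%). Adjusted for a 5% false discovery rate over three endpoints, it gives 88.4% (plan: 88%). Nothing in the sample size rests on the point raised here.

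**Inputs.** Let q be the share of the TACcare arm counted as not treated. Let D be the amount, in SD, by which their change from baseline to 12 weeks is worse than that of engaged patients. The document gives neither, so both are assumptions: q = 10–20% and D = 0.3–0.5. The 14% in the sample-size section is overall attrition, not session non-engagement. The target of 0.6 comes from the Outcomes section; q and D are set against it on the same SD scale.

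**Formula, no true effect, equal arms.** Set both randomised arm means to 0.

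- Engaged TACcare patients average +qD, and non-engaged patients average −(1−q)D.
- Non-engaged moved to control: the enlarged control group averages −q(1−q)D/(1+q). The difference is qD + q(1−q)D/(1+q) = 2qD/(1+q).
- Non-engaged dropped: the difference is qD − 0 = qD.

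| q | D | Moved: 2qD/(1+q) | Dropped: qD |
|---|---|---|---|
| 0.10 | 0.3 | 0.06/1.10 = 0.055 | 0.03 |
| 0.10 | 0.5 | 0.10/1.10 = 0.091 | 0.05 |
| 0.20 | 0.3 | 0.12/1.20 = 0.100 | 0.06 |
| 0.20 | 0.5 | 0.20/1.20 = 0.167 | 0.10 |

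The largest value is 0.167/0.6 = 28% of the target. With D = 0 every entry is 0; with D negative every sign reverses.

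**Why D must be a difference in change.** Primary Outcomes Analyses includes baseline as a time point and takes the group-by-time interaction as the treatment effect. A deficit S that is the same at baseline and at 12 weeks produces a gap of 2qS/(1+q) at both times. The interaction is their difference, which is 0.

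**False positives.** With 20,000 simulated trials per setting, no effect, 68 per arm and non-engaged patients moved to control (7 or 14 of 68, the nearest whole numbers), a two-sided 5% t-test on such a change rejected as follows.

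| q | D | As-treated | Intention-to-treat |
|---|---|---|---|
| 10% | 0.3 | 6.2% | 4.9% |
| 10% | 0.5 | 8.4% | 4.8% |
| 20% | 0.3 | 9.1% | 5.0% |
| 20% | 0.5 | 16.3% | 4.5% |

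This is a two-sample test, not the planned mixed model, so the rates are a guide only.

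**The case against.** The case against is that this is one of four supplementary checks. The sentence about refining conclusions introduces the whole list, no decision rule depends on the as-treated result, and an analysis plan not at hand may define treated. All of that stands. It limits the importance of the point, and the missing definition is not part of it. It does not make a comparison by treatment received a test of the randomised one.

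A reader might infer that any excess of sicker or more depressed patients among the non-engaged biases the result. The planned model does not support that: a persistent difference in level cancels, and only a different change over time matters. The sample-size paragraph, which speaks of comparing groups at 12 weeks, could be read as a comparison of levels, but Primary Outcomes Analyses is explicit about the interaction.

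A reader might also infer that the document shows how many patients fail to engage, or that they do worse. It shows neither, and two features limit non-engagement: patients in pre-contemplation are not enrolled, and the intervention period can be extended to complete 12 sessions.

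Finally, a complier-average estimate might be taken as unbiased and free of assumptions. It is not. Patients who attend some sessions receive some treatment, so a high session threshold strains the assumption that assignment acts only through engagement. Patients are also unblinded. Control patients are shielded in part, since "the care coordinator for the intervention and control arm will not be the same person", but the protocol accepts that renal providers might start managing symptoms in controls and plans outreach to physicians. Non-adherence is near one-sided, not strictly so.

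**Conclusion.** The point holds as a minor one. The as-treated comparison breaks randomisation, answers a different question, and is not a valid check on the robustness of the intention-to-treat result. With no true effect it could favour TACcare by about 0.05–0.17 SD if non-engaged patients are moved to control, or 0.03–0.10 SD if they are dropped. Those figures rest on assumed non-engagement of 10–20% and an assumed 12-week change 0.3–0.5 SD worse in that group. The bias is absent if engagement is unrelated to prognosis and reverses if better-off patients disengage.

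It would go too far to say that the trial's main conclusion is at risk: the primary test, the sample size and the stated power do not depend on this analysis. It would also go too far to say that the as-treated result carries no information; it is enough that it does not test robustness.

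**What to change.** Replace the as-treated analysis with a complier-average causal effect, labelled supplementary. Use the randomised arm as the instrument and a prespecified definition of engagement, for example any session attended, with higher session thresholds as a check. With one-sided non-adherence, the estimate is the intention-to-treat difference divided by the share engaged. If that difference is zero, so is the estimate, whatever the prognosis of those who do not engage.

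The numerator should be a treatment-policy intention-to-treat contrast that keeps outcomes after discontinuation where they were collected. It should not be the estimate described under Intercurrent events. That estimate already aims at the outcome had discontinuation not occurred, so dividing it by the share engaged would correct twice: at 80% engaged, 1/0.80 = 1.25, an inflation of 25%.

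State as assumptions that assignment affects outcome only through engagement and that controls have almost no access to TACcare. The cost is a small extra analysis from session records, one additional intention-to-treat contrast, and wider confidence intervals.
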